#### Quality of life

Assessed at weeks 0, 6, 10 and 14 using PedsQL 4.0 Generic Core Scale and PedsQL 3.0 Gastrointestinal Symptoms Scale.^46 47^

#### School absence

Monitored via a self-designed questionnaire.

#### Anthropometrics

Body weight (kg) and height (cm) measured at baseline and week 14.

### Statistical analysis

Continuous data will be presented as mean±SD if normally distributed and as median with IQR otherwise. Categorical data will be presented as proportions. The 95% CI will be calculated for all primary and secondary parameters, with significance set at α=0.05. The primary outcome, attrition rate, is defined as the proportion of participants completing the study. Attendance at 100%, ≥75% and ≥50% of acupuncture sessions will be reported. Feasibility is confirmed if ≥70% of participants complete the study while attending ≥75% of sessions, informing a future RCT design. Secondary feasibility outcomes include consent rate, satisfaction and personnel capacity. Consent rate is the proportion of approached participants who provided consent, with age distribution reported as mean±SD or median (IQR). Reasons for non-participation will be described. Satisfaction scores (5-point Likert scale) at weeks 6, 10 and 14 will be summarised, visualised with bar plots and analysed descriptively. Personnel requirements will be summarised.

A table will summarise acupuncture points. Safety analysis includes AE frequency. Efficacy, assessed as the proportion no longer meeting Rome IV criteria, will be analysed using McNemar’s test. Due to the study design, no efficacy claims can be made without a control group.

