Written informed consent (parents/guardians and children ≥12 years)	Clotting disorders or recent history of thrombocytopenia
	Immunocompromised children
	Established diagnoses of autism spectrum disorders
	Established major psychiatric disorders or a history of abuse
	Rash or active local infection over an acupuncture point

* Rome IV criteria (fulfilled for ≥2 months before diagnosis) for IBS in children and adolescents include all of the following: (1) Abdominal pain at least 4 days per month associated with one or more of the following: (a) Related to defecation. (b) A change in frequency of stool. (c) A change in the form (appearance) of stool. (2) In children with constipation, the pain does not resolve with resolution of the constipation (children in whom the pain resolves have functional constipation, not IBS). (3) After appropriate evaluation, the symptoms cannot be fully explained by another medical condition.

† Insufficient symptom management is defined as the presence of ≥1 of the Rome IV criteria for FC *despite* medical management by a physician.

‡ Defined as meeting ≥2 of the following criteria during the 2-week run-in period despite receiving treatment with PEG (min. 0.2 g/kg/day).

FC, functional constipation; PEG, polyethylene glycol.

From a global health perspective, the burden of FC on healthcare and healthcare costs is significant. Due to the protracted nature of childhood FC, it accounts for up to 25% of visits to paediatric gastroenterologists in the USA.^7^ Annual healthcare costs related to FC vary between studies but are estimated to be three times higher in children with FC than for children without constipation, accounting for an additional cost of up to $3.9 billion/year in the USA alone.^8 9^

Initial treatment consists of non-pharmacological and pharmacological interventions.^10^ Non-pharmacological interventions involve education and demystification, toilet training (with a reward system), and keeping a defecation diary. First-line pharmacological treatment involves oral osmotic laxatives, preferably polyethylene glycol (PEG).^10^ Osmotic laxatives are considered safe, but adherence to PEG is generally low.^11^ In rare cases, surgical interventions such as antegrade continence enemas or colonic resections with or without diverting ostomy are performed as a last resort.^12^

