### Sample size calculation

This feasibility pilot study evaluates an intervention protocol not previously studied. A sample size of 18 patients was deemed sufficient to assess the primary objective, based on consultation with a statistician.^39 40^ The sample size calculation considers a significance level of alpha=0.05, power of 0.8, estimated feasibility of 0.9, and a lower bound of 0.7 for study exclusion. This sample size minimises patient exposure while providing enough data to inform the future RCT.

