#### Visit 1: eligibility check (t=−2)

Patients will be assessed for eligibility based on inclusion and exclusion criteria. Baseline data, including anthropometrics, will be recorded. Patients will receive instructions on defecation diaries and escape medication usage. A 2-week baseline run-in period follows, where participants continue PEG treatment (min. 0.2 g/kg/day). Children who meet the modified Rome IV criteria for FC (adjusted for the duration of the run-in period) will be enrolled to receive acupuncture (table 1).^3^

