#### Visit 2: screening and first acupuncture treatment (t=0)

After the run-in period, eligibility is confirmed based on the diary information, according to the modified Rome IV criteria. A bowel clean-out regimen (bisacodyl or enemas) is initiated for 2–3 days (box 1). On successful bowel clean-out, the first acupuncture session begins.

Box 1Escape medication

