#### Efficacy

Treatment success, defined as resolution of FC per Rome IV criteria at the end of the intervention (EOI).^3 37^ Rome IV criteria will be assessed by the investigator at the screening visit (visit 1) and at the EOI visit. For the EOI assessment, the criteria will be assessed over the last 4 weeks of the acupuncture intervention, or, in the event a participant discontinues the study prematurely within 4 weeks, over the intervention period. Other efficacy endpoints will be assessed via symptom diaries, the endpoints, including quality of life and school absence, are based on a previously published core outcome set^45^:

Defecation frequency (bowel movements/week).Stool consistency (Bristol Stool Scale).Painful defecation (yes/no).Faecal incontinence frequency (episodes/week).Withholding behaviour (yes/no).Abdominal pain (yes/no, Visual Analogue Scale score).Spontaneous bowel movements (>24 hours after escape medication).Time between acupuncture and defecation.Bowel movements <24 hours after acupuncture.Escape medication use and effect.

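### McNemar's test on Rome IV resolution has one discordant cell fixed at zero by the entry criteria, so its p-value counts resolutions without regard to how many children were treated

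*Protocol article*

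**What the plan says.** The protocol article's Statistical analysis section sets the test for treatment success: "Efficacy, assessed as the proportion no longer meeting Rome IV criteria, will be analysed using McNemar’s test". It does not say whether the exact, continuity-corrected or uncorrected form is meant, and it gives no reference resolution rate. The same section states: "The 95% CI will be calculated for all primary and secondary parameters, with significance set at α=0.05". It closes by ruling out efficacy claims because there is no control group.

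Baseline status is fixed by enrolment. Under Visit 1: "Children who meet the modified Rome IV criteria for FC (adjusted for the duration of the run-in period) will be enrolled to receive acupuncture". Under Visit 2, before the first session: "After the run-in period, eligibility is confirmed based on the diary information, according to the modified Rome IV criteria". The footnote to Table 1 sets the threshold: "Defined as meeting ≥2 of the following criteria during the 2-week run-in period", while on PEG.

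Under Efficacy, treatment success is resolution of functional constipation by Rome IV at the end of the intervention (EOI), judged over the last 4 weeks of treatment. On timing, that section says: "Rome IV criteria will be assessed by the investigator at the screening visit (visit 1) and at the EOI visit".

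**The concern.** McNemar's test asks whether changes in one direction outnumber changes in the other. It needs both directions to be possible. Here the entry criteria remove one of them: a child who does not meet the criteria in the run-in is not treated, so no treated child can move from not constipated to constipated. The test then compares the number of resolutions with a cell that is zero by design, and its null hypothesis becomes that no child ever resolves.

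That null can fail for reasons unrelated to acupuncture. Children are selected on two weeks of symptoms, which invites regression to the mean. A bowel clean-out precedes the first session, PEG continues, escape medication is available, and the end assessment covers a different window (4 weeks against 2). A p-value below 0.05 next to a treatment success figure could be read as evidence of benefit, although it would show only that some children resolved. It would also add nothing to the design of the later RCT, which is what the pilot is meant to inform.

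**Working it through.** **The plan's own figure.** The protocol gives no calculation for this test. Its only sample size, 18, is for feasibility: "A sample size of 18 patients was deemed sufficient to assess the primary objective". That figure is reproduced by (1.96 + 0.84)² × 0.9 × 0.1 / (0.9 − 0.7)² = 17.66, rounded up to 18. It neither supports nor weakens the present point, but it supplies N.

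**Inputs.** N = 18 (Sample size calculation); α = 0.05 (Statistical analysis), taken as two-sided because the sidedness is not stated; all children positive at baseline (Table 1, Visits 1 and 2). Let b be the number who change from meeting to not meeting the criteria, and c the number who change the other way. By design c = 0.

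**Formulas with c = 0.**
- Exact two-sided: p = 2 × 0.5^b
- Uncorrected chi-square, 1 df: (b − c)²/(b + c) = b
- Continuity-corrected chi-square, 1 df: (b − 1)²/b

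N appears in none of them.

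| Resolutions b | Exact p | Corrected p | Uncorrected p |
|---|---|---|---|
| 4 | 0.125 | 0.134 | 0.046 |
| 5 | 0.0625 | 0.074 | 0.025 |
| 6 | 0.031 | 0.041 | 0.014 |

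The threshold is therefore 6 resolutions for the exact and corrected forms and 4 for the uncorrected form. With 18 children these are 33% and 22%.

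**Independence from N.** With b = 6, the exact p is 0.031 at N = 10, 18, 50, 100 and 1000. The proportion and its Clopper-Pearson interval do distinguish these cases: 6/18 = 33.3% (13.3% to 59.0%), and 6/100 = 6% (2.2% to 12.6%). The two results differ greatly and share one p-value.

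**How often the threshold would be reached without any acupuncture effect.** The protocol gives no such resolution rate, so a range is assumed. For X ~ Binomial(18, π):

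| Assumed π | Pr(X ≥ 6) | Pr(X ≥ 4) |
|---|---|---|
| 10% | 0.6% | 10% |
| 20% | 13% | 50% |
| 30% | 47% | 84% |
| 40% | 79% | 97% |

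**If one cell entry were not zero.** Suppose one child were classed negative at visit 1 and positive at EOI, so c = 1. The exact p is 0.070 at b = 7, and at b = 8 it is 2 × (1 + 9)/2⁹ = 0.039. Eight resolutions would then be needed, and there would still be no meaningful reference rate.

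**The case against.** Three objections deserve an answer.

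First, the structural zero depends on which two time points are compared, and the Statistical analysis section does not name them. The Efficacy section places the first assessment at visit 1, before the run-in, and the insufficient-management criterion needs only one Rome IV criterion, so a child could in principle be negative at visit 1 and positive in the run-in. Table 2 also lists Rome IV assessments at other visits, and a comparison of two post-baseline visits would have no fixed zero. This stands as a qualification only. The Participants section requires a Rome IV diagnosis, which makes such a child rare. The endpoint is tied to EOI, and no post-baseline pair is mentioned.

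Second, the consequence is small. Efficacy is secondary; the sample size, the primary criterion, the interim review and the step to an RCT rest on feasibility; efficacy claims are disclaimed; and a 95% CI is already planned. All of this stands and sets the weight of the point.

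Third, a reader might infer that entry selection guarantees a significant result, or that the result is the same whatever the sample size or treatment effect. The documents support neither inference. Entry selection fixes the direction of change, not the number of changes. The chance of reaching six depends on N and on the true resolution rate: at an assumed 10% it is 0.6% with 18 children and 94% with 100. Low rates cannot be dismissed, since these children remain symptomatic after at least 3 months of medical management and the Introduction describes a persistent condition. Only once the number of resolutions is known is the p-value the same whatever N is and whatever caused them.

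**Conclusion.** Wrong as written, of minor severity. On the natural baseline-to-EOI reading, the planned test has a null of zero resolution and a p-value set by the count of resolutions alone: 6 for the exact or continuity-corrected form, 4 for the uncorrected form, at any N. It cannot say whether the success proportion is higher than would be expected without acupuncture. The conclusion rests on two assumptions: the comparison runs from a baseline at which all treated children meet the criteria, and the test is two-sided. The 10% to 40% range for resolution without an acupuncture effect is assumed and serves only to show that significance may be improbable or likely. The primary feasibility conclusion is not affected, and the protocol makes no claim of efficacy that would have to be withdrawn.

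**What to change.** In the Statistical analysis section, delete McNemar's test. Let the proportion no longer meeting Rome IV at EOI, with the 95% CI that the section already plans, be the only efficacy summary for treatment success, without a p-value. With 18 children the interval should be exact (Clopper-Pearson): for example 6/18 = 33% (13% to 59%) or 9/18 = 50% (26% to 74%). If a test is nevertheless wanted, it would need a non-zero reference rate, justified and fixed before the data are seen. The change is one sentence, needs no further data, and loses no information.

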### Interim analysis

An interim analysis will be conducted after 10 participants have completed the study, including follow-up, to evaluate feasibility. This unblinded analysis will assess attrition rate, consent rate, patient and parent satisfaction, and retention rate. The interim findings will be discussed with the research team to determine whether the study should continue as planned. The principal investigator will make the final decision regarding trial continuation and will report this decision to the METC.

### Ethics and dissemination

#### Ethics approval

Ethics approval was granted by the METC of the Amsterdam UMC (NL87083.018.24). This study will be conducted according to the principles of the Declaration of Helsinki (64th WMA General Assembly, Fortaleza, Brazil, October 2013) and in accordance with the Medical Research Involving Human Subjects Act.

#### Registration details

ClinicalTrials.gov (NCT06836362) and CCMO (NL-OMON57236).

#### Dissemination

The results of this pilot study will be presented at national and international conferences and published in an international medical journal.
